This is a mixed methods research study including the collection of data from patient's medical notes, interviews and quality of life questionnaires in accordance with the schedule of assessments (SoA, Annex I). This study also involves the implementation of an auditory-visual sensory stimulation package in the cardiac ICU at ICHT to participants enrolled in the study. Digital photos will be shown continuously at the patient bedside after cardiac surgery and will always have reference to time and date. Additionally, videos will be played throughout participants' stay in ICU for at least three times per day and upon participant request. Videos will be also played when participant show signs of ICU delirium with the aim of reducing delirium incidence and improve overall better health outcomes. Simultaneously, primary outcomes measures (CAM-ICU, a routine delirium screening measure) will be collected by the research team, as this is evaluated twice a day as per usual standard of ICU practice, with the aim of assessing whether patients develop delirium during their stay in ICU.

Interviews with patients and families/friends will be held in three different occasions. The first one will be on the same day as ICU discharge, the second interview will be on the day of hospital discharge and the third one will be carried out up to a month following hospital discharge during their clinical follow-up appointment. Where possible, family members/friend and patient's interviews will be conducted together (dyadic interviewing), but the possibility of performing interviews separately will be given, so that participants feel able to discuss opinions freely without influence. Nurses' interviews will be held as a one-off and after they have provided direct care to participants who received the proposed intervention.

Each patient will be followed up daily on the wards and once at the monthly follow-up clinic up after ICU discharge, where cognitive and emotional assessments will be performed to evaluate delirium outcomes. The research team will also collect relevant information from participant's medical notes if any complications post ICU discharge arise during inpatient and follow-up stages.

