In occasions where participants are unable to consent or have lost their capacity to consent more than once whilst in ICU (e.g., delirium), their participation in the study will be considered by approaching their personal consultee. If their participation in the study resumes, videos / photos will be played at the patients' bedside during the planned intervention schedule. Upon delirium diagnosis, the last video played will be shown again to patients with the aim of promoting a reduction in ICU delirium. In the unfortunate eventuality of an urgent clinical deterioration (e.g., urgent induced coma due to mechanical ventilation requirements) that may happen whilst in ICU, their participation in the study will also resume considering their initial consent form signed before surgery and after seeking prior agreement with their personal consultee. In these situations, the Patient Regaining Capacity Consent Form will be collected at a later stage and after patients have re-gained capacity to express their wishes.

For patients who lose mental capacity after hospital discharge, they will be formally discussed with the CI and withdrawn from the research study. The study team will communicate the decision to participants and appropriately document it on medical notes.

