## **6. STUDY ASSESSMENTS**

### **6.1. ASSESSMENT AND FOLLOW UP**

#### **STUDY INTERVENTION**

The intervention will require family members/friends (selected by patients) to self-record short videos (during the preoperative stage) based on a carefully drafted guided script divided into two parts: a) Reorientation (discussing date/time/surroundings, family members on the video); b) Reassurance (providing comforting/supportive messages). Videos will be recorded either with a video-recorder device (provided by the research team) in the pre-operative clinic or at home using a personal smartphone. At a later stage, videos will be sent to an encrypted NHS email and securely uploaded in line with ICHT Information Governance to a password-protected iPad, which will also facilitate family-patient video calls in ICU. In addition, patients will be requested to select personal pictures pre-operatively, which will be also sent to the PI's encrypted NHS email and securely uploaded into a special digital photo frame with reference to time and date.

Digital photos will be shown continuously at the patient's bedside for 12 hours a day (between 8am to 8pm) and different family videos will be played three times at specific hours of the day (9am, 2pm and 7pm) throughout their stay in ICU. Additionally, videos will be also played upon patient request and last video shown that day will be re-played. In occasions when patients develop ICU delirium and considering personal consultee's agreement, the last video shown to participants will be re-played and patients will be closely monitored. This will help the research team to understand if the combination of personal pictures and family videos impacted patients' orientation and reassurance and if, ultimately, promoted the reduction of ICU delirium. The PI will be responsible for setting up the required equipment and delivering the intervention alongside ICU nurses as illustrated in the study diagram below (Annex XI).

The draft guided script of reorientation and reassurance messages was initially developed based on published research and considering patients' memories from their lived ICU experience(s) [15]. Subsequently, it was further refined within a lay focus group of patient and public members (with ICU lived experience) and reviewed by an expert panel comprising two critical

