care consultants, two critical care nurses and one clinical academic research nurse (Annex XIII). Family members and friends will be requested to not deviate from the draft script order of events and to frequently mention the patient's name at the beginning/end of sentences when recording the video. They will be also asked to provide personalised messages in the second part of the video and to use simple terms equivalent to a 5th-grade reading level. The research team expects that part A) of the video to be similar between study participants, but part B) tailored to each individual participant.

Additionally, as previously agreed and supported by the critical care nursing lead for the ICU at Hammersmith Hospital, all critical care nurses will contribute to the study by filling in a daily checklist (Annex XII). This checklist will help the research team to understand the impact of the study intervention and if participants developed ICU delirium. Moreover, as per standard ICU practice at ICHT, patients following cardiac surgery will be closely monitored and primary outcomes regularly collected by critical care nurses.

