## ANNEX I - Schedule of Assessments (SoA)

| Exam                                                                                 | Pre-treatment
(Clinic) | Treatment
(ICU) |                |                |                | Inpatient follow-up
(Ward)  | Outpatient follow-up
(Clinic) |
|--------------------------------------------------------------------------------------|---------------------------|--------------------|----------------|----------------|----------------|--------------------------------|----------------------------------|
| Study Days                                                                           | -D60 to D0                | D0                 | D1             | D2             | D3             | D4, D5, D6, D7, D8,
D9, D10 | D30                              |
| Informed Consent                                                                     | X                         |                    |                |                |                |                                |                                  |
| Cardiac surgery                                                                      |                           | X                  |                |                |                |                                |                                  |
| ICU Family Intervention                                                              |                           |                    | X              | X              | X              |                                |                                  |
| CAM-ICU and RASS                                                                     |                           | X                  | X              | X              | X              |                                |                                  |
| Vital Signs (Heart Rate, Blood Pressure, Respiratory Rate, Temperature, Saturations) | X             | X      | X  | X  | X  | X                  | X                    |
| Dyadic Interviews                                                                    |                           |                    |                |                | X  | X                  | X                    |

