|----------|-------------------------------------------------------------------|--------------------------------------------------------------------------------------------------------------------------------------------------------------------------------------------------------------------------------------------------------------------------------|
| 1 | Were any visual/auditory aids removed prior to sleep?             |  Yes  No                                                                                                                                                                                                                       |
| 2 | From a nurse’s perspective, how many hours did the patient sleep? | _____ hours                                                                                                                                                                                                                                                                    |
| 3 | Did the patient request to watch the video overnight?             |  Yes  No
If “Yes”, how many times: ____                                                                                                                                                                                     |
| 4 | Did the patient develop delirium overnight?                       |  Yes  No
4a. If “Yes”, was the video played again?
 Yes  No
4b. If “Yes”, did it improve delirium status?
 Yes  No |
| 5 | Was the iPad plugged in to charge overnight?                      |  Yes  No                                                                                                                                                                                                                       |

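### The delirium replay rule plays the last video shown, so an overnight replay states an out-of-date time and, from midnight to 9am, the previous weekday and post-operative day

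*Protocol*

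**What the plan says.** Protocol Section 6.1 (Study Intervention) sets the daily schedule: "different family videos will be played three times at specific hours of the day (9am, 2pm and 7pm) throughout their stay in ICU". The videos are recorded before surgery.

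For delirium there is an extra showing. Section 6.1 says that, if the personal consultee agrees, "the last video shown to participants will be re-played and patients will be closely monitored". Section 4.6 (Patients Regaining Consent) gives the same rule: "Upon delirium diagnosis, the last video played will be shown again to patients with the aim of promoting a reduction in ICU delirium". Neither passage restricts the replay to certain hours or names a night version.

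Annex XIII, part A (Reorientation), has the family member state an approximate clock time (9am, 2pm or 6pm), the day of the week and the number of days since the operation. Of the order of the script, Section 6.1 says: "Family members and friends will be requested to not deviate from the draft script order of events".

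Night replays are foreseen. The 8pm to 8am checklist in Annex XII asks "Did the patient develop delirium overnight" (item 4), then whether the video was played again (4a) and whether delirium improved (4b).

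**The concern.** Part A of the video exists to tell the patient what time and day it is and how long ago the operation was. These statements are fixed at recording and are right only near the scheduled showing. The delirium rule separates the video from its scheduled slot. No video is scheduled between 7pm and 9am, so that is where the gap grows largest.

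Followed as written, the rule can tell a delirious patient in the small hours that it is early evening on the day before. Section 6.1 says that observing these replays will help show whether the pictures and videos affected orientation and reassurance. A night replay judged under item 4b would carry orientation cues that are themselves wrong. In a study of how to deliver this package, such a rule should be corrected before it is carried into later work.

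**Working it through.** The protocol gives no figure to reproduce here; the check is clock arithmetic.

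**Inputs**
- Play times 9am, 2pm and 7pm: Section 6.1.
- Times stated in the videos, 9am, 2pm and 6pm, plus weekday and post-operative day: Annex XIII, part A.
- Replay rule, last video shown: Sections 4.6 and 6.1.
- Night form, 8pm to 8am: Annex XII.
- Intervention days: the row "ICU Family Intervention" in Annex I is marked D1, D2 and D3.

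**Formula.** Age of the stated time = replay time − time stated in the last scheduled video, with hours after midnight counted as 24 + hour. The stated day is wrong if midnight has passed and the 9am video has not yet been shown.

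| Replay at | Last video played | Age, scripted as 6pm | Age, script corrected to 7pm | Stated day |
|---|---|---|---|---|
| 8pm | 7pm | 20 − 18 = 2 h | 20 − 19 = 1 h | correct |
| midnight | 7pm | 24 − 18 = 6 h | 24 − 19 = 5 h | previous day |
| 8am | 7pm | 32 − 18 = 14 h | 32 − 19 = 13 h | previous day |
| just before 9am | 7pm | just under 33 − 18 = 15 h | just under 33 − 19 = 14 h | previous day |

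**Daytime, for comparison.** From 9am to 2pm the age is 0 to 5 h, and from 2pm to 7pm again 0 to 5 h. From 7pm to 8pm it is 20 − 18 = 2 h at most. The day is correct throughout.

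**Post-operative day.** From midnight to 9am the video gives a number one too low.

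**Conditions.** These ages assume that the 7pm video was shown. If it was missed and the 2pm video was the last, the age is 20 − 14 = 6 h at 8pm and 32 − 14 = 18 h at 8am. On the Annex I schedule no video precedes D1, so the first affected night is the one after D1.

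**The evening slot.** The 9am and 2pm slots agree between Section 6.1 and Annex XIII. The evening slot differs by 19 − 18 = 1 h. Correcting the script to 7pm shortens each overnight age by that hour and leaves the wrong-day window unchanged.

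**The case against.** Several points on the other side have force.

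- **Consultee gate.** Replay needs the consultee's agreement. Under Section 4.6 (Personal Consultees) that person is introduced after surgery when capacity is lost and is given time to consider. A first episode in the small hours may not lead to an immediate replay. This stands in part: Section 4.5 has the consultee chosen earlier, and later episodes may already be covered.
- **Unseen diagram.** Section 6.1 refers to Annex XI for delivery, and that figure is not available here. It may contain a night provision. The point rests on the rule as worded in Sections 4.6 and 6.1.
- **Approximate time.** Annex XIII asks only for an approximate time. That excuses the one-hour evening mismatch, but not 14 hours or the wrong day.
- **Recorded message.** Part B of the script tells the patient that the message is a recording. That helps, but does not supply the real time or day.
- **Data already separated.** Day and night checklists are separate, so most outdated replays can be told apart from near-correct ones. This stands.

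Three stronger readings are tempting but not supported. A reader might infer that nothing at the bedside corrects the video at night, because Section 6.1 shows the photos "for 12 hours a day (between 8am to 8pm"). Section 3, however, says "Digital photos will be shown continuously at the patient bedside after cardiac surgery and will always have reference to time and date", and neither passage says whether the frame's clock stays visible overnight. A reader might turn the affected hours into a fixed share of the ICU stay. That share depends on the hour of ICU discharge, which varies between patients. A reader might also apply the delirium incidence in Section 1.1 to the 12 patients. That incidence covers all hours and says nothing about how many would meet the rule overnight.

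**Conclusion.** The point holds as a defect in how the intervention is specified. A delirium replay between 8pm and 8am states a time 2 to 14 hours old, or 1 to 13 hours if the script is corrected to 7pm. From midnight until the 9am video it also states the previous weekday and a post-operative day one too low. This assumes that the 7pm video was shown and that Annex XI does not override the written rule.

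The weight is limited. The number of overnight replays is unknown and depends on consultee agreement. A reader might infer that patients would be harmed; the documents give no evidence of that, and Section 6.1 provides for close monitoring. No sample size, endpoint or analysis changes. It is still worth correcting, because a stated rule works against the stated purpose of part A and the remedy costs almost nothing. The 6pm/7pm difference is a minor wording slip.

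**What to change.** Amend Sections 4.6 and 6.1 for delirium replays from 8pm until the 9am video, choosing one of these:

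1. **Preferred.** The nurse states the actual time, date and post-operative day with the replay. This needs no recording and only moments of nursing time.
2. **Alternative.** Play an undated clip that keeps the greeting by name, the speaker's identity and the statements that surgery is over and the patient is in intensive care. The cost is one extra short recording per family, so 12 × 1 = 12 clips at the planned recruitment.

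Starting the replay at part B is only a fallback. It needs no recording, but it drops those cues, which stay true at any hour and matter most during delirium.

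As a minor correction, use one evening time in Section 6.1 and Annex XIII. Moving the showing to 6pm would spare re-recording but leave the overnight age at 2 to 14 h. Keeping 7pm means checking evening videos already made.

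The wording change is small, but it alters delivery of the intervention and so should go through the amendment route in Section 9.

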### **3.1. STUDY OUTCOME MEASURES**

The study's endpoint, similar to the primary objective of this research study, is to assess the feasibility and acceptability of implementing a nurse-led intervention in ICU, using family-focused sensory stimulation to improve delirium outcomes in patients undergoing cardiac surgery.

This study secondary outcome measures are to develop an innovative nurse-led tool to improve ICU delirium outcomes after cardiac surgery in ICHT and its acceptance amongst patients, family members/friends and critical care staff.

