| Nursing interviews                                                                   |                           |                    |                |                | X  |                                |                                  |
| Montreal Cognitive Assessment                                                        |                           |                    |                |                |                | X                  | X                    |
| Generalised Anxiety Disorder Questionnaire-7                                         |                           |                    |                |                |                | X                  | X                    |
| Patient Health Questionnaire-9                                                       |                           |                    |                |                |                | X                  | X                    |
| CAM                                                                                  |                           |                    |                |                |                | X                  | X                    |

Vital signs to be collected at least one time during pre-treatment, inpatient follow-up, and outpatient follow-up stages; and daily highest/lowest vital signs during ICU stay.

Participants and family members/friends will be approached for dyadic interviews three times: day of ICU discharge, day of hospital discharge and up to one month post ICU discharge to discuss the intervention and assess delirium complications. Whether possible, interviews will be performed together, but single interview option will be provided.

Critical care nurses will be approached for one single interview to evaluate intervention acceptability, useability, and possible study limitations.

All quality-of-life questionnaires (QoL) are to be performed by participants one time during the inpatient stage and another time at the outpatient follow-up clinic appointment.

Short-term delirium outcomes post ICU discharge will be evaluated by performing daily CAM assessments during the inpatient period and once at the follow-up appointment.

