## ANNEX XII – Critical Care Nurse’s checklist

Table 1. Nursing Checklist Daytime

| N | Nursing Checklist Daytime (8am – 8pm)                                                               | Tick as appropriate                                                                                                                                                                                                                                                            |
|----------|-----------------------------------------------------------------------------------------------------|--------------------------------------------------------------------------------------------------------------------------------------------------------------------------------------------------------------------------------------------------------------------------------|
| 1 | Did the patient have any unknown visual/auditory impairment?                                        |  Yes  No                                                                                                                                                                                                                       |
| 2 | Were any visual/auditory aids (eg. glasses/hearing aids) in place during the intervention delivery? |  Yes  No  N/A                                                                                                                                                                                          |
| 3 | Was the family intervention delivered 3 times during the day (8am-8pm)?                             |  Yes  No
Times: 1. ____:____; 2. ____:____; 3. ____:____                                                                                                                                                                    |
| 4 | Did the patient express any verbal/non-verbal emotions when watching the video?                     |  Yes  No
If “Yes”, please specify: ____                                                                                                                                                                                     |

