| 5 | Did the patient look at the digital photo frame during the day?                                     |  Yes  No
If “Yes”, how many times: ____                                                                                                                                                                                     |
| 6 | Did the intervention impact ICU nursing care?                                                       |  Yes  No
If “Yes”, please specify: ____                                                                                                                                                                                     |
| 7 | Was the family intervention delivered without any untoward events (eg., acute distress)?            |  Yes  No
If “No”, please specify: ____                                                                                                                                                                                      |
| 8 | Did the patient request to watch the video more than 3 times a day?                                 |  Yes  No
If “Yes”, please specify the total number of times: ____                                                                                                                                                           |
| 9 | Did the patient develop delirium during the day (8am-8pm)?                                          |  Yes  No
9a. If “Yes”, was the video played again?
 Yes  No
9b. If “Yes”, did it improve delirium status?
 Yes  No |

Table 2. Nursing Checklist Night-time

| N | Nursing Checklist Night-time (8pm – 8am)                          | Tick as appropriate                                                                                                                                                                                                                                                            |

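### The endpoint is feasibility of a nurse-led programme, but the PI shares set-up and delivery and the checklist does not record who ran each play, so nurse delivery cannot be separated from PI-supported delivery

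*Protocol*

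**What the plan says.** Section 3.1 gives the study's endpoint as "to assess the feasibility and acceptability of implementing a nurse-led intervention in ICU". Its secondary outcome is the development of a nurse-led tool.

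Under the Study Intervention heading, section 6.1 divides the work differently: "The PI will be responsible for setting up the required equipment and delivering the intervention alongside ICU nurses". The sentence then refers to the diagram in Annex XI, which is not reproduced in the copy available. The part of section 8.4 on reducing bias adds that the PI will not give direct care to study patients.

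The per-play record that the Protocol describes is the nurses' checklist in Annex XII. On delivery it asks the following:

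- Daytime item 3: "Was the family intervention delivered 3 times during the day (8am-8pm", answered yes or no with three clock times.
- Daytime item 6: "Did the intervention impact ICU nursing care", yes or no with free text.
- Daytime item 8: whether the patient asked for more than three showings, and how many in total.
- Daytime item 9a and night-time item 4a: after delirium, "was the video played again".
- Night-time item 3: "Did the patient request to watch the video overnight", with a count.

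Annex I, footnote 3, adds the qualitative arm: "Critical care nurses will be approached for one single interview to evaluate intervention acceptability, useability, and possible study limitations".

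**The concern.** An endpoint about a nurse-led programme needs evidence on what bedside nurses do. The checklist describes delivery in the passive voice. A *Yes* to item 3 looks the same whether the nurse ran all three videos, the PI ran all three, or they shared them. Item 6 has the same gap: a *No* may mean that the programme is light work, or that the PI did the work that day.

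The PI is a funded research fellow who has undertaken not to provide direct care to participants. The PI's time is therefore a research resource, which a ward adopting the programme later would not have. If the study reports good delivery and little burden without saying how much rested on the PI, a later trial or roll-out could be planned on a figure that nurses alone did not achieve. The gap is in the data collected, so an analysis plan cannot close it afterwards.

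**Working it through.** **Is there a figure to reproduce?** No. The Protocol states no delivery percentage, feasibility threshold or power calculation, and section 7 names no delivery rate among its analyses. The check is a reading of the form, followed by an illustration.

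**Reading Annex XII against sections 3.1 and 6.1.** There are nine daytime items and five night-time items. Those touching delivery are daytime 3, 8 and 9a and night-time 3 and 4a. They capture occurrence, clock times or counts. None captures who set up the equipment or who ran the video. The other items cover sensory aids, patient reactions, looking at the photo frame, effect on nursing care, untoward events, sleep, delirium status and charging the iPad. No section shown caps the PI's share, separates PI plays from nurse plays, or defines feasibility on nurse delivery.

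**Number of plays.** 12 patients (section 3) × 3 ICU days marked for the intervention (Annex I, D1 to D3) × 3 scheduled plays a day (section 6.1) = 108. Section 6.1 runs the programme for the whole ICU stay, so the actual total will vary.

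**Form of the distortion.** Let *s* be the share of scheduled plays in which the PI takes part, *p_PI* the delivery rate for those plays, and *p_N* the rate when nurses act alone.

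- Recorded rate = s × p_PI + (1 − s) × p_N
- Distortion = recorded rate − p_N = s × (p_PI − p_N)

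The Protocol gives none of the three values. All of those below are assumptions chosen to show the range.

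With p_PI = 100%, the recorded rate (distortion in percentage points) is:

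| s | p_N = 50% | p_N = 70% | p_N = 90% |
|---|---|---|---|
| 25% | 62.5% (+12.5) | 77.5% (+7.5) | 92.5% (+2.5) |
| 50% | 75% (+25) | 85% (+15) | 95% (+5) |
| 75% | 87.5% (+37.5) | 92.5% (+22.5) | 97.5% (+7.5) |

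Example: 0.50 × 1.00 + 0.50 × 0.70 = 0.85, against 0.70 for nurses alone.

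Item 3 is a whole-day answer. If the three plays are independent, the same example gives 0.85³ = 61% of days with all three delivered, against 0.70³ = 34% for nurses alone.

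**Where the distortion vanishes or reverses.** It is zero if s = 0 or p_PI = p_N. With s = 50%, p_PI = 70% and p_N = 90%, the recorded rate is 0.50 × 0.70 + 0.50 × 0.90 = 80%, which understates nurse delivery by 10 points.

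**The case against.** The strongest reply has four parts.

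1. **Joint delivery is not substitution.** Section 6.1 has the PI working with the nurses, not in their place, and Annex XI may show how tasks are divided. This stands as a limit on any claim about size. It does not fill the gap, because a diagram can assign roles but cannot record who acted at each play.

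2. **The study's question is broader.** The research question in section 2 and the primary objective in section 2.1 ask about delivery in critical care and about introducing the programme, without naming nurses as the deliverers. Nor does section 3.1 define nurse-led as working without research support. This is fair, and it is why relabelling the endpoint is an acceptable alternative fix. As written, though, section 3.1 puts nurse leadership in the endpoint.

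3. **Other sources may show reliance on the PI.** Item 6 has free text, six nurses are interviewed on useability and limitations, and section 4.3 already excludes nurses who took no part in implementation. That exclusion largely covers the choice of interviewees, so no change is needed there. The interviews help only in part: section 6.1 has the PI conduct all of them, so nurses would be describing their reliance on the PI to the PI.

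4. **No reported figure is there to be inflated.** The Protocol sets no fidelity percentage or threshold, and section 6.1 presents the checklist as a means of understanding the intervention's impact and whether delirium developed. This is correct, and it keeps the point modest.

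A reader might infer that feasibility will be overstated, or by a particular amount. The documents do not support either inference, because the PI's share and both delivery rates are missing. Nor do they support the view that the PI's involvement is itself a fault; research support is ordinary in feasibility work.

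**Conclusion.** The point holds in a limited form. The endpoint concerns a nurse-led programme, delivery is shared with the PI, and the checklist does not record the deliverer. As planned, the delivery record cannot separate nurse delivery from PI-supported delivery.

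Nurse-led feasibility and low nursing impact may be overstated. Upward is the likelier direction if the PI is the more reliable deliverer, but that is an assumption. The illustrated range, from +2.5 to +37.5 points with a reversal also possible, reflects assumed inputs and is not an estimate for this study. For item 6 no size can be put on the effect at all.

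No stated calculation changes. This is a worthwhile, inexpensive improvement to data collection, best made before checklists are completed because the information is hard to reconstruct later.

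**What to change.** **Annex XII.** Beside each of the three times in daytime item 3, add two short fields, *set up by* and *delivered by*, each with the options bedside nurse, PI or both. Add the same fields for every requested showing and every delirium replay, by day and by night.

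**Reporting.** Give nurse-delivered plays over scheduled plays as its own line, with PI-delivered and joint plays shown separately. Tabulate item 6 by whether the PI was involved that day.

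**Alternative.** If the split is not to be recorded, reword section 3.1 so that the endpoint is feasibility of researcher-supported delivery.

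**Cost.** A brief tick entry per play and a few table rows. The nurse-delivery figure may come out lower than the pooled one. The PI's role need not change.
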